**Abstract**

**Introduction:** The outbreak of a novel coronavirus (SARS-CoV-2) and associated COVID-19 disease in late December 2019 has led to a global pandemic. It directly leads to high morbidity and mortality, but also results in a devastating effect on the global economy. Nowadays many trials are underway on this disease to evaluate the efficacy of various therapeutic remedies. This study aims at investigating the effect of Traditional Chinese Medicine, maxingshigan-weijing for treating patients with COVID-19.

**Methods and analysis:** This is an open-label, multicenter randomized controlled clinical trial. One hundred and forty patients infected by SARS-CoV-2 will be randomly assigned to the control group or the experimental group ( Traditional Chinese Medicine, TCM group ) in an equal ratio. The patients in control group will receive routine supportive clinically care including the therapies of anti-viral, anti-bacterial and ameliorating the related symptoms, while patients in TCM group will be asked to take traditional Chinese medicine, maxingshigan-weijing for consecutive 14 days in addition to supportive care. All data will be gathered at baseline and on days 3, 7, 10 and 14. The primary outcome measure will be the number of days till at least one of the clinical symptoms (fever, cough, malaise, shortness of breath) improves in the first 14 days of treatment. Secondary outcome measures will include TCM Syndrome Scoring System and the time of negative of SARS-CoV-2 nucleic acid. A laboratory test will be taken before and after treatment to assess the safety of TCM.

**Discussion:** The study may help to identify the the efficacy and safety of Traditional Chinese Medicine, Maxingshigan-weijing in treating COVID-2019.

**Trial registration:** Chinese Clinical Trial Registry, ChiCTR2000030759. Registered on March 13th 2020, <http://www.chictr.org.cn/.>

**Keywords:** SARS-CoV-2, COVID-2019, Traditional Chinese Medicine ( TCM ), Maxingshigan-weijing decoction, Randomized controlled trial, Protocol

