**Sample size**

Based on previous clinical practice of using TCM fought against SARS and H1N1 influenza patients [23], it is estimated the median survival time in the TCM group as 3 days, and 1.5 times longer in the control group. Concerning the analysis of the primary endpoint, the duration of time before improvement of at least one of the common cold-like symptoms (fever, cough, malaise, shortness of breath) , will be estimated using the Kaplan-Meier method, and

the survival curves will be compared between groups using the log-rank test. And this study is designed to detect a statistically significant difference with a level of 5% and a power of 70% (one-sided type-1 error of
[figure not shown]
 =5%，
[figure not shown]
 =30%), so approximately 61 participants in each group will be needed. Thus, under the prediction of a dropout rate of 10%, the sample size of 140 participants will be sufficient to detect a clinically important difference in this trial.

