**Prohibition and permission for concomitant treatment**

All concomitant care and interventions are permitted other than concomitant receipt of any other experimental treatment.

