**INTERVENTIONS**

Maxingshigan-weijing decoction consists of 10 g of Herba Ephedra (Mahuang), 10 g of Amygdalus Communis Vas (Xingren), 45 g of Gypsum Fibrosum (Shigao), 30 g of Rhizoma phragmitis (Lugen), 20 g of Peach kernel (Taoren), 20 g of Winter Melon kernel (Dongguaren), 30 g of Trichosanthes Kirilowii Maxim (Gualou), 12 g of Pericarpium Citri Reticulatae (Chenpi), 12 g of Rhizoma Pinelliae (Jiangbanxia), 12 g of caulis bambusae in taeniis (Zhuru), 30 g of semen lepidii (Tingliz), 15 g of semen lepidii (Shichangpu), 10 g of curcuma zedoary (ezhu) and 5 g of Radix Glycyrrhizae (Gancao). Maxingshigan-weijing decoction will be prepared by TCM pharmacy of the First Affiliated Hospital of Wenzhou Medical University.

Inpatients will be randomly assigned to two groups receiving either Routine supportive care alone which includes Stay in bed, Nasal cannula of oxygen therapy, broad-spectum antibiotics and antivirals, or the combination of Maxingshigan-weijing decoction for continuous 14 days, 200 mL twice a day at 10 AM and 4PM. All participants will be hospitalized so that they could be quarantined and closely observed. What is more, to ensure compliance with the medication, patients will be asked to return the empty wrapping papers. If there will be any remaining medicine, it will be recorded.

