**MEASUREMENTS**

***Primary Outcome***

The primary outcome will be the number of days until the clinical symptom of fever improves in the first 14 days of treatment following randomisation. Fever will be defined as an improvement when the temperature is less than 37℃.

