traditional Chinese and western medicine in the treatment of SARS.

Journal of practical internal medicine of traditional Chinese

medicine,2005.19(6):529.

1. Qing Miao, Xiaodong Cong, Bing Wang et. al. Recognition and

reflection of TCM on pneumonia caused by novel

coronavirus.2020,61(2):1-4.

2. JSM P, D P, Yuen KY ea. The Severe Acute Respiratory Syndrome. New Engl J 71. Med.. 2003; 249: 2431-41.

[figure not shown]

|  | **Pre** | **Research Phase** | | | | | | | | | | | | | | **Follow-up** | |
| --- | --- | --- | --- | --- | --- | --- | --- | --- | --- | --- | --- | --- | --- | --- | --- | --- | --- |
| **Time point** | **D0** | **D1** | **D2** | **D3** | **D4** | **D5** | **D6** | **D7** | **D8** | **D9** | **D10** | **D11** | **D12** | **D13** | **D14** | **D7** | **D14** |
| **Research activities** |  |  |  |  |  |  |  |  |  |  |  |  |  |  |  |  |  |
| Enrollment | × |  |  |  |  |  |  |  |  |  |  |  |  |  |  |  |  |
| Eligibility screen | × |  |  |  |  |  |  |  |  |  |  |  |  |  |  |  |  |
| Informed consent | × |  |  |  |  |  |  |  |  |  |  |  |  |  |  |  |  |
| Randomization | × |  |  |  |  |  |  |  |  |  |  |  |  |  |  |  |  |
| **Intervention activities** |  |  |  |  |  |  |  |  |  |  |  |  |  |  |  |  |  |
| TCM + Supportive care |  | × | × | × | × | × | × | × | × | × | × | × | × | × | × |  |  |
| Supportive care |  | × | × | × | × | × | × | × | × | × | × | × | × | × | × |  |  |
| **Baseline assessments** |  |  |  |  |  |  |  |  |  |  |  |  |  |  |  |  |  |
| Socio-demographics | × |  |  |  |  |  |  |  |  |  |  |  |  |  |  |  |  |
| Medical history | × |  |  |  |  |  |  |  |  |  |  |  |  |  |  |  |  |
| Differentiation | × |  |  |  |  |  |  |  |  |  |  |  |  |  |  |  |  |
| Routine inspection | × |  |  |  |  |  |  |  |  |  |  |  |  |  |  |  |  |
| Concomitant medication | × | × | × | × | × | × | × | × | × | × | × | × | × | × | × | × | × |
| **Outcome assessments** |  |  |  |  |  |  |  |  |  |  |  |  |  |  |  |  |  |
| Syndromes Relief | × |  |  | × |  |  |  | × |  |  | × |  |  |  | × |  |  |
| Coronavirus nucleic acid test | × |  |  | × |  |  |  | × |  |  | × |  |  |  | × |  |  |
| TCM Syndrome Scoring System | × |  |  | × |  |  |  | × |  |  | × |  |  |  | × | × | × |

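### The primary outcome is counted in days, but it is assessed only on days 3, 7, 10 and 14, which is too coarse to report a 1.5-day difference in medians

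*Protocol*

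**What the plan says.** - **Outcome.** The Primary Outcome section states: "The primary outcome will be the number of days until the clinical symptom of fever improves in the first 14 days of treatment following randomisation". The event rule is: "Fever will be defined as an improvement when the temperature is less than 37℃". The Abstract defines the outcome more widely: "The primary outcome measure will be the number of days till at least one of the clinical symptoms", naming fever, cough, malaise and shortness of breath. Both versions are counts of days within the first 14.
- **Assumed effect.** The Sample size section says "it is estimated the median survival time in the TCM group as 3 days", with the control median 1.5 times longer (read here as 4.5 days). It names Kaplan-Meier estimation and the log-rank test. Statistical Analysis repeats the log-rank test. Neither section mentions interval censoring or how an event is dated.
- **Assessment days.** The Abstract says "All data will be gathered at baseline and on days 3, 7, 10 and 14". In Fig. 2 the row nearest to the primary outcome, "Syndromes Relief", is marked at D0, D3, D7, D10 and D14. The routine inspection row, which presumably carries temperature because Safety outcomes lists it in the routine examination, has no other days in the treatment period. Treatment, concomitant medication and adverse events are marked daily. No efficacy row is.
- **Setting.** Interventions says: "All participants will be hospitalized so that they could be quarantined and closely observed".

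**The concern.** The visits leave gaps of 3, 4, 3 and 4 days, all at least twice the 1.5-day difference the trial is sized for. A fever that ends on day 4 is first seen as ended on day 7. The only event days that visit data can yield are 3, 7, 10 and 14, so an assumed control median of 4.5 days cannot be observed as such. Ordinary Kaplan-Meier treats the visit day as the true event day. If medians are reported from it, their difference reflects the spacing of the visits as well as the treatment. Fig. 2 uses daily marks where daily capture is meant, so this is a stated schedule and not merely detail left for a later plan.

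**Working it through.** **Inputs.** Medians 3 and 4.5 days, one-sided 5%, power 70%, 61 per group and 10% dropout (Sample size); 14 days of observation (Study design, Primary Outcome); visits on D3, D7, D10 and D14 (Abstract, Fig. 2). Two assumptions are not in the Protocol: exponential event times, and dating each event to the first visit on or after it.

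**1. The Protocol's own figure.** Let k = (1.645 + 0.524)² = 4.706.
- Schoenfeld: 4k / (ln 1.5)² = 18.82 / 0.1644 = 114.5, so 115 events.
- The 14-day event probabilities are 1 − 2^(−14/3) = 0.961 and 1 − 2^(−14/4.5) = 0.884, mean 0.922. This gives 114.5 / 0.922 / 2 = 62.1 per group.
- Freedman without censoring: 25k = 117.6, so 118 events, or 59 per group.
- The stated 61 lies between the two. Since 61 / 0.9 rounds up to 68 per group (136 in all), 140 covers dropout.

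The sample size therefore reproduces, and it takes event times as known.

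**2. Probability of an event by each visit**, 1 − 2^(−t/median):

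| | D3 | D7 | D10 | D14 |
|---|---|---|---|---|
| TCM (median 3) | 0.500 | 0.802 | 0.901 | 0.961 |
| Control (median 4.5) | 0.370 | 0.660 | 0.786 | 0.884 |

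**3. Where the observed median falls.** With 61 patients, the median is the first visit by which at least 31 have improved.
- TCM: P(Bin(61, 0.500) ≥ 31) = 50%, so the median is D3 in half of trials and D7 in the other half.
- Control: P(Bin(61, 0.370) ≥ 31) = 1.9% for D3, and P(Bin(61, 0.660) ≥ 31) = 99.5% by D7. The median is D7 in 97.6% of trials.
- Difference of 4 days: 0.50 × 0.976 = 49%. Difference of 0: 0.50 × 0.976 + 0.50 × 0.019 = 50%.

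Simulation of 3,000 trials agrees: 0 days in 50.0%, 4 days in 48.2%, −4 in 1.3%, and 3 or 7 in 0.6%.

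**4. Visit schedule against daily recording** (exponential, 61 per group):

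| | Visit days | Daily | Exact times |
|---|---|---|---|
| Mean difference in medians (days) | 1.9 | 1.5 | 1.5 |
| SD (days) | 2.1 | 1.1 | – |
| Central 95% range (days) | 0 to 4 | about 0 to 4 | −0.4 to 3.6 |
| One-sided log-rank power | 68% | 69% | 70% |

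Daily recording gives a difference of 1 or 2 days in about 67% of trials.

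**5. Sensitivity.**
- *Shape.* With Weibull shape 1.5 or 2 and the same medians, the visit-day difference is 0 or 4 days in every simulated trial, split about evenly. Daily recording gives 1 or 2 days in 80% to 89%. Power is 92% (visits) against 95% (daily) for shape 1.5, and 98% against 99% for shape 2.
- *Position of the medians.* The even split arises because the assumed TCM median lies exactly on D3. At the same ratio and with exponential times, medians of 2.5 and 3.75 give 0 days in 24% and 4 days in 74%. Medians of 3.5 and 5.25 give about 75% and 20%.

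**The case against.** The strongest reply is that the planned analysis is a log-rank test and both groups share one visit schedule. The test therefore keeps its size (simulated one-sided type I error 5.0%) and loses only one or two points of power in the exponential case. This stands. A reader might infer that the trial is underpowered or its test invalid because of the visits; the calculations do not support that.

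A second reply is that medians appear only as sample-size inputs, and that the reporting of estimates and the dating of events may be settled in an analysis plan not shown here. That stands in part. No later plan can recover days that were never recorded, and the recording days are fixed in this document. Sampling noise also matters: even daily data give a range of about 0 to 4 days at this sample size. The schedule roughly doubles the SD; it is not the only source of imprecision.

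Third, the 3 and 4.5 day medians belong to improvement of any one of four symptoms, whereas the Primary Outcome section concerns fever alone, for which no medians are given. The size is therefore shown only for the wider definition, although the same visit days apply to both.

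A reader might also infer that one reading at a visit decides the event, and that antipyretics bias the comparison between groups, since "All concomitant care and interventions are permitted other than concomitant receipt of any other experimental treatment". The documents do not establish this. They give no number of readings and do not mention antipyretics. Temperature is an objective measure, and Study design and Blinding state that outcome assessors are blinded. The Protocol does set no sustained period for improvement, but no bias by group is shown.

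**Conclusion.** The point holds as a mismatch between an outcome counted in days and a schedule that observes it at gaps of 3 to 4 days. Under the assumptions stated (exponential times, 61 per group, events dated to the visit where first seen), a reported difference in Kaplan-Meier medians would be 0 or 4 days in about 98% of trials. The 1.5 days assumed in the design could not appear, and the SD would be 2.1 days instead of 1.1. That a result of 0 or 4 is certain, or always evenly split, would be too strong: it is not quite universal in the exponential case, and the split depends on the TCM median falling on D3. The harm is to the precision and meaning of the reported times. The log-rank comparison stays usable. This should be corrected, but it does not undermine the primary test.

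**What to change.** Add a daily D1 to D14 row for temperature, and for the other primary symptoms if the wider definition is kept, to Fig. 2 and to the case report form. Date the event to the first day that meets the Protocol's own improvement criterion. All participants are inpatients, so this should be feasible, although the Protocol does not say that daily ward charts exist or will be used.

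For patients already enrolled without daily values, estimate event times with an interval-censored method and do not report Kaplan-Meier medians computed from visit days. Such a method also accepts a mix of daily and visit-based data. The proportions improved by each visit can be reported without any dating assumption.

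Concomitant medication is already recorded daily in Fig. 2, so antipyretic use can be examined in a sensitivity analysis. Whether improvement must be sustained is for the investigators to decide. A new requirement of that kind would redefine the primary endpoint late in recruitment: Trial status gives version 2.0 as October 2020, with completion expected by the end of December 2020. Nothing in the document fixes its form.

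The cost is one extra daily line on the case report form, and an analysis that must handle mixed recording intervals for patients enrolled before the change.

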**Background**

In December 2019, an unexplained pneumonia broke out in Wuhan City, Hubei Province. And it was identified and named COVID-2019 (Corona Virus Disease-2019) by the World Health Organization ( WHO ) on 30th January 2020[1]. Unfortunately, this virus quickly spread throughout China[2] and had been identified as a pandemic and a health emergency of global concern by WHO[3]. What is even more frightening is that the virus has spread with astonishing speed around the world, many people in Europe and United States have suffered from COVID-2019[4].

SARS-CoV-2 is the causative pathogen of COVID-19, identified as the seventh type of coronavirus to infect humans [5]. Six other kinds of coronaviruses are known to cause human disease, including severe acute respiratory syndrome coronavirus (SARS-CoV) and Middle East respiratory syndrome coronavirus (MERS-CoV) which had caused two large-scale pandemics in the past two decades [6,7]. According to the genome characteristics, coronavirus is separated into four genera: α-CoV, β-CoV, γ-CoV, and δ-CoV [8]. Deep sequencing revealed that this novel coronavirus shares 79.6% sequence identity with SARS-CoV and belongs to β-CoV [9].

In the past two decades, human fought with SARS-CoV and MERS-CoV hardly, they firstly and fastly used those broad-spectrum antiviral drugs, including interferons, ribavirin, and cyclophilin inhibitors, in addition to supportive care[10,11,12]. The second category of candidate antivirals clinicians chose, through screening of chemical libraries that comprise large numbers of existing drugs or databases that contain information on transcriptional signatures in different cell line, consisted of mycophenolic acid, lopinavir, chloroquine and so on[13,14]. Furthermore, widely usage of Traditional Chinese Medicine (TCM) to treat these two infectious diseases was another option for Chinese doctors, especially in the treatment of patients infected with SARS-CoV in 2002-2003[15]. It was reported that the patients with SARS-CoV infection had benefited from TCM treatment, including amelioration of side effect of conventional therapeutics[16,17,18].

Faced with COVID-2019, because of no clinically specific drugs currently[19], doctors choose the drugs mentioned above empirically but the clinical efficacy is unsatisfactory and uncertain. During these challenging and unprecedented times, the current clinical guideline in China suggest both conventional medicine and TCM should be used for the treatment of patients with infection of SARS-CoV-2[20].

Based on these evidence and experience, there is a general expectation that TCM would be a valuable weapon in the armory against SARS-CoV-2. So an open-label, multicenter randomized controlled study will be carried out to evaluate the efficacy and safety of Traditional Chinese Medicine in treating COVID-2019. This study is conducted in Wenzhou city, Zhejiang Province, because Wenzhou is one of the worst-hit cities outside hubei province by COVID-2019.

**METHODS**

**Study design**

This is an open-label, multicenter, randomized controlled, comprehensive treatment clinical study, with outcome assessors and data analysts blinded to the group assignment. Eligible participants with Mild and Moderate Pneumonia caused by SARS-CoV-2 will be randomly assigned to either the experimental ( Traditional Chinese Medicine + Routine supportive care ) or the control group ( Routine supportive care ) in an equal proportion. Routine supportive care remains the major treatment, including the therapies of anti-viral, anti-bacterial and ameliorating the related symptoms[21]. The study consisted of three phases: a screening period, a treatment period of 14 days, and a follow-up period of 2 weeks. Fig. 1 briefly shows the study flow chart, and Fig. 2 enumerates the treatment schedule and outcome measures. The study adheres to the Standard Protocol Items: Recommendations for Intervention Trials (SPIRIT 2013) checklist [22].

**Participants and Recruitment**

Participants will be recruited from 3 hospitals, the First Affiliated Hospital of Wenzhou Medical University, the Second Affiliated Hospital of Wenzhou Medical University and Wenzhou Center Hospital. These 3 hospitals are appointed to treat patients with COVID-19. To recruit target subjects, the study researchers will send a message to every inpatient when they are diagnosed with SARS-CoV-2. If the inpatients are eligible and interested in taking part in the study, they will be fully informed of the project information including the study procedures, potential benefits and risks. Written informed consent includes provisions for use of study data and biological specimens in future researches will be obtained from the patient or their substitute decision-makers before the allocation. All participant have the right to withdraw from the study at any time.

**Inclusion criteria**

1. Participants are 18-85 years of age, either male or female.
2. Diagnosed as positive for severe acute respiratory syndrome coronavirus 2 (SARS-CoV-2)
3. Symptomatic. Mild (mild clinical symptoms without signs of pneumonia in chest X-ray), and Moderate (fever or [respiratory](../../../../C:/Users/[name]/Downloads/%25E6%259C%2589%25E9%2581%2593/Dict/8.9.0.0/resultui/html/index.html" \l "/javascript:;) [symptom](../../../../C:/Users/[name]/Downloads/%25E6%259C%2589%25E9%2581%2593/Dict/8.9.0.0/resultui/html/index.html" \l "/javascript:;) with signs of pneumonia in chest X-ray) .
4. Signed the informed consent before treatment.
5. Agreed not to enroll in any other clinical trials.
6. Inpatients

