**Coronavirus nucleic acid test**

The coronavirus nucleic acid test by reverse transcription polymerase chain reaction ( RT-PCR ) will be conducted at the baseline and day 3, day 7, day 10 and day 14 of the study intervention. The time ( in days ) of the respiratory tract sample and blood specimens SARS-CoV2 RT-PCR to be negative for two consecutive times based on the first testing time will be defined as primary outcome.

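### Patients already RT-PCR negative at baseline may enter the trial and, on the stated definition, would count as viral conversions on day 0, before treatment starts

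*Protocol*

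**What the plan says.** **Entry.** Protocol, Inclusion criteria, item 2 reads "Diagnosed as positive for severe acute respiratory syndrome coronavirus 2 (SARS-CoV-2"). It names no assay, specimen or date, and sets no interval to randomisation. Item 3 adds that patients must be symptomatic ("Symptomatic. Mild (mild clinical symptoms without signs of pneumonia in chest X-ray), and Moderate"), and item 6 that they are inpatients. None of the six exclusion criteria concerns a negative baseline test or time since diagnosis. Under Participants and Recruitment, "the study researchers will send a message to every inpatient when they are diagnosed with SARS-CoV-2".

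**Outcome.** Under Coronavirus nucleic acid test, the RT-PCR "will be conducted at the baseline and day 3, day 7, day 10 and day 14 of the study intervention". The outcome is the time in days for respiratory and blood specimens "to be negative for two consecutive times based on the first testing time". Nothing is said about a patient who is negative at baseline.

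**Schedule.** In Fig. 2 the row "Coronavirus nucleic acid test" stands under the outcome assessments, with a mark at D0. Randomisation is also at D0, and both treatment rows start at D1.

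**Status.** The Abstract lists this outcome as secondary: "Secondary outcome measures will include TCM Syndrome Scoring System and the time of negative of SARS-CoV-2 nucleic acid". The test section stands under the secondary outcomes but calls it the primary outcome.

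**The concern.** The baseline test is one of the tests that can supply the two consecutive negatives, and a positive baseline result is not a condition of entry. Together these allow an event to be recorded before the patient has taken any of the study treatment. Such an event says nothing about the treatment. It adds the same early value in both arms, which pulls the comparison towards no difference, lowers power, and shortens the reported time to negativity relative to patients who were still positive when randomised.

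This is more than a detail left for an analysis plan. The Protocol itself defines the outcome, and following that definition as written gives the poorer result.

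**Working it through.** **1. The passages side by side.** Take a symptomatic inpatient with an earlier positive result whose respiratory and blood samples are negative at D0 and D3.

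| Question | Protocol text | Result |
|---|---|---|
| Eligible? | Inclusion items 2, 3 and 6; no exclusion applies | Yes |
| Which tests count? | Baseline, D3, D7, D10, D14 | D0 and D3 are the first two |
| When is conversion? | Two consecutive negatives, dated by the first | Day 0 |
| When does treatment start? | Fig. 2 | D1 |

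The event precedes exposure.

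**2. The plan's own sample size.** Inputs from the Sample size section: medians 3 and 3 × 1.5 = 4.5 days, one-sided 5%, power 70%.

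- Events (Schoenfeld): 4 × (1.645 + 0.524)² / (ln 1.5)² = 4 × 4.706 / 0.1644 = 114.5, so 115.
- Probability of an event by day 14, exponential times: 1 − 2^(−14/3) = 0.961 and 1 − 2^(−14/4.5) = 0.884.
- Per group: 115 / (0.961 + 0.884) = 62.3. Freedman's formula gives 118 events, or 59 per group without censoring. The plan's 61 lies between.
- Dropout: 61 / 0.9 = 67.8, so 68 per group or 136 in all, close to the stated 140.

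The figure reproduces. It concerns symptom improvement, so the present point does not touch it. No sample size is stated for the viral outcome.

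**3. How many patients.** The D0-negative share q is not in the Protocol. Assume 5% to 20%: 140 × 0.05 = 7 and 140 × 0.20 = 28 patients with an event at day 0, leaving 133 to 112 informative.

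**4. Effect on the median.** Assume exponential clearance with a control median of 9 days in D0-positive patients (an assumption). With a share q at time 0, the median m solves q + (1 − q)(1 − 2^(−m/9)) = 0.5, so m = 9 × log2[2(1 − q)]. For q = 10%, 9 × log2(1.8) = 7.6 days. For q = 20%, 9 × log2(1.6) = 6.1 days.

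**5. Effect on power.** Simulation with 70 per arm, the same 9-day control median, a rate ratio of 1.5 (assumed for this outcome) and visits at D3, D7, D10 and D14. D0-negative patients are either counted as events at time 0 or left out.

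| Test | q | D0-negatives counted at day 0 | D0-positive only |
|---|---|---|---|
| Wilcoxon (planned for secondary outcomes), two-sided 5% | 0% | 49% | – |
| | 10% | 37% | 46% |
| | 20% | 24% | 42% |
| Log-rank, one-sided 5% | 0% | 65% | – |
| | 10% | 54% | 60% |
| | 20% | 45% | 57% |
| | 30% | 38% | 55% |

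A repeat of the Wilcoxon rows with fresh random numbers agreed to within about 3 percentage points. The simulation lets a first negative at D14 count, although no later test could confirm it. Disallowing this lowers every Wilcoxon figure by a few points and leaves the pattern unchanged.

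**6. Effect on false positives.** With no true effect, rejection was 0.043 to 0.046 for the Wilcoxon test and 0.046 to 0.064 for the log-rank test, with no trend in q.

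**The case against.** **Recruitment is tied to diagnosis.** A reader might infer that an old diagnosis is enough for entry. The Protocol does not support that: patients are contacted when diagnosed and must be symptomatic inpatients. This stands, and it makes D0-negative patients less common. But it governs contact rather than randomisation and sets no limit on the interval, and symptoms do not show that the RT-PCR is still positive.

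**It is a possibility, not a fact.** This also stands. The text permits such patients; it does not show that any entered.

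**The dating rule is ambiguous.** The reference to the first testing time could mean the first of the two negatives or the origin of the time scale. The first is the natural reading. The other still leaves baseline as a test day and gives no rule for a patient negative there.

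**An analysis plan could restrict the analysis set.** It could. The Protocol's definition nevertheless admits day-0 conversions, so the restriction belongs beside it.

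**A false difference between arms.** With 14 D0-negative patients in 140, the arms differ by 6 or more with probability 0.157 (hypergeometric), and a reader might take this as a risk of a spurious finding. It is only the chance of an uneven split. The test's error rate already covers chance imbalance, and step 6 shows it stays near 5%.

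**A threat to the primary outcome.** The stray label "to be negative for two consecutive times based on the first testing time will be defined as primary outcome" might suggest one. The Abstract and the section's placement make the outcome secondary.

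**Conclusion.** The point holds as a limited one. The Protocol allows D0-negative patients to enter and, read literally, dates their conversion to day 0, before treatment. The consequence is dilution, lost power and a misleadingly short conversion time in this one secondary outcome. In the Wilcoxon illustration the loss is 12 points at 10% D0-negative (49% to 37%) and 25 points at 20% (49% to 24%). Analysing D0-positive patients only limits it to 3 and 7 points (46% and 42%).

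These sizes rest on an assumed D0-negative share, 9-day median and rate ratio of 1.5, none of which the Protocol gives for viral clearance. If no patient is negative at D0, nothing is lost. There is no systematic advantage to either arm and no inflation of false positives. The fever or symptom primary outcome and the figures of 61 per group and 140 in total are unaffected.

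**What to change.** In the section Coronavirus nucleic acid test, state that:

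- time to negativity is analysed in patients with a positive respiratory RT-PCR at D0, whenever they were enrolled;
- time is counted from randomisation;
- only tests from D3 onward can supply the first of the two negatives;
- the number of D0-negative patients is reported by arm.

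The D0 sample is already scheduled and D0 status is a baseline characteristic, so the restriction does not depend on treatment and the randomised comparison within the subset is kept. Because recruitment began in March 2020 and Version 2.0 is dated October 14, 2020, the rule must cover patients enrolled before and after that version.

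The cost is a few sentences and a somewhat smaller analysis set for this outcome (133 to 112 of 140 at the assumed shares). No eligibility change is needed. Requiring a positive test within a window such as 72 hours would still admit patients negative at D0, would alter the population for a primary outcome that is not affected, and has no basis in the Protocol for the figure chosen.
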